### Randomization

To explore secondary objectives 3 and 4 using a factorial design, QoL questionnaire order, and spontaneous QoL completion will be randomized 1:1:1:1 using a minimization technique stratified according to center, cancer location, sex, and age.

Patients will be randomized in one of the following four arms (Table 1): (1) Arm A: MVQOLI then QLQ-C15 PAUL and QUAL-E, evaluation every month; (2) Arm B: QLQ-C15 PAL, MVQOLI and QUAL-E, evaluation every month; (3) Arm C: MVQOLI then QLQ-C15 PAL and QUAL-E, evaluation every month and spontaneous QoL completion; and (4) Arm D: QLQ-C15 PAL, MVQOLI and QUAL-E evaluation every month and spontaneous QoL completion.

**Table 1 T1:** Follow-up for QoL and data collection according to randomized arms

	Baseline		Follow-up	
	**D1^a^**	**Between** **D1 and D3^b^**	**Before every consultation until death (J30+/-3 days)**	**If necessary according to randomized allocated arm (notebook)**

**Collected data and order of administration for QoL questionnaires**				

	**Arms**	**Arms**	**Arms**	**Arms**

Consent	A/B/C/D			

Questionnaires: QLQ-C15, MVQOLI and QUAL-E	A/B/C/D	A/B/C/D	B and D	

Questionnaires: MVQOLI, QLQ-C15 and QUAL-E			A and C	

Questionnaires: MVQOLI, QLQ-C15				D and C

Performance Status, Performance Palliative Scale	A/B/C/D	A/B/C/D	A, B, C, D	

Vital signs, pain (EVA)	A/B/C/D	A/B/C/D	A, B, C, D	

Care (Oncology, Psychology, and so on)	A/B/C/D	A/B/C/D	A, B, C, D	

Responsiveness question	A/B/C/D	A/B/C/D		D and C

^a^D1: First day, the day where the first QoL questionnaires will be completed; D3: 3 days after the first day administration

^b^Can be done D1 at the end of the day if the first was done early in the day

^c^Only MVQOLI and QUAL-E

The above randomization was chosen to explore methodological aspects to optimize QOL tools in the end-of-life setting.

It will allow us to assess the occurrence of an order effect on QoL level by investigating a halo effect and/or a framing effect. Since every patient should complete three questionnaires (MVQOLI, QUAL-E, and the QLQ-C15 PAL), completion of the first questionnaire could influence responses for the following questionnaires, resulting in different QoL levels. Moreover, this effect could be differential depending on the completion order. Since QUAL-E needs a face to face interview, it will be completed by the patient at the end for each arm.

The second randomization will investigate the added value of spontaneous QoL completion to capture clinically important changes in QoL that could have occurred between two planned QoL assessments.

For each allocated group a specific case report form (CRF) will be produced with the corresponding order of QoL questionnaires to prevent changes in completion order (that is, 'cross-over') after the randomization.

Furthermore, the date and time of completion for each QoL questionnaire will be collected. This will allow us to check the order of completion used by the patients.

### Evaluation criteria

#### End of life QoL questionnaires

Within the framework of this study, three questionnaires will be used: QLQ-C15 PAL, QUAL-E, and MVQOLI. The McGill questionnaire was not retained since it assesses the QoL during a short period (quality of life during the 2 days before questionnaire completion).

The EORTC QLQ-C15 PAL reflects patients' QoL during the previous week and investigates two domains (symptoms and physical functioning). An additional item assesses patients' perception of overall QoL. This is a shortened version of the EORTC QLQ-C30, which aims to prevent missing QoL data due to patients' health status. Scores will be calculated using the same algorithm as that used in the QLQ-C30 methodology [22]. Scores will therefore range from 0 (poor QoL) to 100 (best QoL). [23,24].

Taking into account the limited number of dimensions investigated by the EORTC QLQ-C15 PAL, we have selected the QUAL-E and MVQOLI to complement QoL evaluations at the end of life. These two questionnaires dedicated to the end of life have been methodologically validated in their original language, English [25,26].

Twenty-five items and one overall question constitute the QUAL-E questionnaire. Five dimensions can be explored: life completion (particularly through contributions to others), relations with the healthcare system (knowledge and participation of patients in therapeutic decisions), preparation for the end of life, symptom severity (by capturing symptom impact), and affective social support. This questionnaire should be completed during a face-to-face interview. Every question is scored on a 5-point Likert scale [25,26].

The MVQOLI, developed by Byock *et al*. in 1995 [14,26], includes 15 items in the shortened version and 25 items in the original version. The shortened version was selected since Byock *et al*. previously showed a good correlation (r = 0.93) between these two versions, suggesting that the shortened version does not seem to be associated with a loss of information [14]. This tool explores five dimensions: symptoms (experience of the physical discomfort associated with progressive disease), functional activities (perceived ability to perform usual functions and activities), interpersonal (degree of investment in personal relationships and the perceived quality of one's relations with family and friends), wellbeing (contentment or lack of contentment with self), and transcendence (degree of experienced meaning and purpose in life). It helps professionals to identify factors that affect patient QoL at the end of life. The items related to the 'evaluation' range from -2 to +2, those for the 'satisfaction' range from -4 to +4 and those for 'importance' range from 1 to 5. Each dimension of the questionnaire will be calculated using specific items related to'satisfaction', 'evaluation', and 'importance'.

The score is the sum of the 'evaluation' and 'satisfaction' scores multiplied by the 'importance' score. The total score is obtained by summing each score related to each dimension divided by 10 and then adding 15 points. If the score is negative QoL is poor. The score reflects the impact of each dimension for patients.

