### Sample size for secondary objectives

The main endpoint to assess the added value of spontaneous QoL completion is the proportion of patients who report at least one Minimal clinically important difference (MCID) using the Jaeschke transition question.

The minimal clinically important difference is defined as an improvement or a deterioration of 5% in the theoretical QoL score range [23].

With a bilateral alpha type one error of 1% (Bonferroni adjustment for multiple comparisons) a power of 90%, and the following hypotheses:

H0: 70% of patients report an MCID before death in arms A and B

H1: 90% of patients report an MCID before death in arms C and D

It will be necessary to have 243 patients with at least two completed QoL questionnaires between two follow-ups representing 65.4% of the 372 patients included for the primary objective.

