5. To define a period of 'end of life' QoL dimensions that strongly correlate with a patient's health status (physical dimensions, fatigue, pain) should decrease at the end of life, whereas dimensions (psychological, spirituality) more related to the end of life could remain stable and/or could slowly improve. These patterns in longitudinal QoL changes will be captured using mixed model analysis of variance for repeated measurement, and time until definitive QoL score deterioration.

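### For the MVQOLI part of objective 5, the importance-weighted dimension score cannot by itself separate a change in patient state from a change in what matters to the patient

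*Protocol article*

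**What the plan says.** The section on end-of-life QoL questionnaires gives the MVQOLI item ranges as -2 to +2 for evaluation, -4 to +4 for satisfaction and 1 to 5 for importance. The dimension score is defined by "The score is the sum of the 'evaluation' and 'satisfaction' scores multiplied by the 'importance' score", and the total by "The total score is obtained by summing each score related to each dimension divided by 10 and then adding 15 points". The stated meaning is that "The score reflects the impact of each dimension for patients".

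Under Completion of QoL questionnaire, all patients fill in the questionnaires monthly until death. Nothing says that importance is carried forward from the first form.

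Two thresholds for change appear. Under Sample size for secondary objectives, "The minimal clinically important difference is defined as an improvement or a deterioration of 5% in the theoretical QoL score range". Under Longitudinal analyses, TUDD uses a fall of at least 5 points from the score at inclusion.

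Objective 5 (item 5 of the secondary analyses) expects physical dimensions, fatigue and pain to fall near death, while psychological and spiritual dimensions "more related to the end of life could remain stable and/or could slowly improve". Mixed models and TUDD are to pick up this pattern.

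**The concern.** The score answers one question and objective 5 asks another. The score measures impact, that is, state multiplied by how much the dimension matters at that moment. Objective 5 uses dimension trajectories to mark a period in which physical state declines and psychological or spiritual state does not. If priorities shift as death approaches, the product moves even when the patient's experience and satisfaction do not.

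The direction depends on the patient's state. Rising importance raises the score of a satisfied patient and lowers that of a dissatisfied one. Falling importance does the reverse and can hide a real decline. What is at stake is whether an MVQOLI trajectory in objective 5 can be attributed to state.

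**Working it through.** **Inputs** (End of life QoL questionnaires): evaluation E from -2 to +2, satisfaction S from -4 to +4, importance I from 1 to 5, five dimensions, constant 15. Thresholds: 5% of range (Sample size for secondary objectives) and 5 points (TUDD, Longitudinal analyses).

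**Check of the reading against the plan's own constant.**
- (E + S) × I has extremes ±(2 + 4) × 5 = ±30. The lowest total is 5 × (-30)/10 + 15 = 0 and the highest is 30.
- The other possible reading, E + S × I, has extremes ±(2 + 4 × 5) = ±22 and gives a total from 4 to 26.
- The added 15 puts the total on exactly 0 to 30 under the first reading, so (E + S) × I is what is meant.

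**Thresholds on a dimension.** The range is 60, so 5% is 3 points. The TUDD threshold is 5 points on the score as described. The article does not say that MVQOLI is rescaled. If it were put on 0 to 100, 5 points would equal 5 × 60/100 = 3 raw points, so the two columns below cover both cases.

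**Effect of importance alone.** With E and S fixed, the change is |E + S| × |change in I|. Among the 5 × 9 = 45 integer pairs (E, S), |E + S| equals 6, 5, 4, 3, 2, 1, 0 in 2, 4, 6, 8, 10, 10, 5 pairs.

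| Change in I | Share reaching 3 points | Share reaching 5 points |
|---|---|---|
| 1 step | \|E+S\| ≥ 3: 20/45 = 44% | \|E+S\| ≥ 5: 6/45 = 13% |
| 2 steps | \|E+S\| ≥ 2: 30/45 = 67% | \|E+S\| ≥ 3: 20/45 = 44% |

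**Examples.**
- Apparent decline: symptoms with E + S = -3 and importance from 3 to 5 go from -9 to -15, a fall of 6. With importance held at 3 the change is 0.
- Apparent gain: transcendence with E + S = +4 and importance from 3 to 5 goes from 12 to 20. With importance held at 3 the change is 0.
- Hidden decline: symptoms worsen from E + S = -2 to -4 while importance drops from 4 to 2. The score is -8 both times. With importance held at 4 it goes from -8 to -16, a fall of 8.

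**Total score.** One step in one dimension moves it by at most 6/10 = 0.6, against 5% of 30 = 1.5. One dimension can contribute at most 6 × 4/10 = 2.4, so two give 4.8, and a 5-point change needs importance shifts in at least three dimensions. The total is much less sensitive.

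**The case against.** The strongest reply is that the weighting is deliberate. The article says the score expresses impact, and on that construct a dissatisfied patient who cares less about function really is less affected by it. The English tool is described as validated, and the study's purpose is to adapt and validate it. This stands: there is no scoring error, and the product must remain the MVQOLI score.

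Other parts of the reply also stand.
- A reader might take 44% or 67% as the share of patients affected. The documents do not support that. The figures weight all answer combinations equally, and neither the frequency nor the direction of importance shifts is given.
- A reader might apply the 3-point figures to TUDD. TUDD as written uses 5 points and also requires the fall to be definitive or followed by dropout, so a passing shift in importance does not count.
- A reader might think the comparison of spontaneous completion is affected. Its endpoint relies on the Jaeschke transition question, which is the patient's own answer and not the product.
- Because the sign differs between satisfied and dissatisfied patients, effects on a group mean may partly cancel.

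It can also be said that component analyses belong in the statistical analysis plan. That is fair as to detail. But the article itself fixes the score, the models and the inference drawn for objective 5, and the mismatch between score and inference is visible there. The planned factorial and item response analyses serve construct validity and do not address it.

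**Conclusion.** The point holds as a limit on interpretation in one secondary objective. In the MVQOLI part of objective 5, a change in a dimension's product score cannot be attributed to state alone. A one-step importance shift is enough for a 5-point change in 13% of the score grid, and a two-step shift in 44%. At 3 points the shares are 44% and 67%. This rests on importance being rated again on each monthly form, which follows from the completion schedule but is not stated outright, and on integer item scores.

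It would go too far to conclude that the MVQOLI evidence, or objective 5 as a whole, cannot be interpreted. QLQ-C15 PAL and QUAL-E are also followed over time and are not described as importance-weighted. Fatigue and pain, named in objective 5, are not MVQOLI dimensions. The calculation shows what can happen, not how often it will. This is a cheap improvement, not a defect in the primary validation.

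**What to change.** Keep the product as the MVQOLI score for validation and as the main longitudinal score. For the MVQOLI part of objective 5, add to both the mixed models and TUDD a sensitivity analysis using (E + S at each visit) × (importance at inclusion). This keeps the -30 to +30 scale and the same thresholds. Describe importance over time for each dimension. Where the two analyses disagree, report that the change may reflect importance and do not attribute it to state alone.

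Two alternatives are best avoided. The unweighted sum E + S should not be allowed to overrule the instrument's own score, since the documents give it neither validation nor a threshold. The 5-point threshold should not be applied to it either, because its scale runs only from -6 to +6.

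The items are already collected, and the analysis plan is still to be written before database lock. The cost is one extra analysis and one descriptive series for each of five dimensions, and a more cautious reading of some product-score changes.

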### Completion of QoL questionnaire

The QoL questionnaires will be completed before randomization and then every month until death in a time driven design fashion.

Using test-retest methodology, the QLQ-C15 PAL, MVQOLI, and QUAL-E questionnaires will be completed 3 days after the first completion at baseline and before randomization [27].

Though a maximum delay of 15 days is usually allowed between completions to check reproducibility, since these patients have a specific end-of-life profile with sometimes a rapid deterioration in general health status, a maximum delay of 3 days was chosen to minimize the 'risk' of changes in health status.

Since the QUAL-E questionnaire should be completed using a direct interview; patients should complete it last to prevent social desirability bias on QLQ-C15 PAL and MVQOLI evaluations [27].

In order to prevent missing QoL data [28], if a patient is unable to complete questionnaires due to poor health status, QLQ-C15 PAL and MVQOLI could be completed with the help of a proxy (from the medical team) who will have to record the patient's answers without interpretation [29]. A specific item will be completed to take this information into account for the longitudinal analysis of QoL.

All patients will complete QoL questionnaires every month until death.

In arms C and D, depending on patients' health status or perceived QoL, patients will be free to complete the QLQ-C15 PAL and MVQOLI questionnaires (spontaneous QoL completion in an event drive design) between two planned evaluations. A patient CRF including QLQ-C15 PAL and MVQOLI questionnaires, the date of completion, the perception of QoL changes using the Jaescke transition question [30]), and a space for free comments will be created. This booklet will be given to the patients after randomization.

The QoL questionnaires will be administered in a homogeneous way by the same person, a nurse specialized in palliative care, a psychologist, or if necessary a clinical research assistant (CRA), throughout the patient follow-up until death.

Completed questionnaires should be returned to one of the CRAs assigned to the study. In order to deal with holidays, a minimum of two full-time CRAs will be required and identified for each participating center (Table 2).

**Table 2 T2:** Center's participation agreement

Organization	City
Cancer care center Paul Papin	Angers, France

Cancer care center Léon Bérard	Lyon, France

Cancer care center Georges François Leclerc	Dijon, France

University hospital center Jean Minjoz	Besançon, France

Cancer care center Henri Becquerel	Rouen, France

Hospital center	Cholet, France

Cancer care center Val d'Aurelle-Paul	Montpellier, France

Cancer care institute Bergonié	Bordeaux, France

Cancer care center Oscar Lambret	Lille, France

Cancer care center François Baclesse	Caen, France

Cancer care institute curie	Paris, France

University hospital center	Angers, France

Original CRF and QoL questionnaires will be kept by the Paul Papin Center; while a copy will be kept on site. Postal delivery could be allowed.

If a patient does not want to or cannot complete QoL questionnaires, a note will be made on the unfilled questionnaire with a brief explanation. An item to collect reasons for non-completion should be also completed by CRAs.

Other data will be collected: demographic data, medical history, medical follow-up (social, psychological, pain, cancer treatment), clinical status, and Jaeschke transition question to define minimal clinically important difference for patients in this setting [30].

### Methodology

#### Translation of the English questionnaire

First step

The QUAL-E and MVQOLI were translated between May 2010 and July 2010 by the national '*Qualité de vie et cancer*' clinical research platform which had selected national experts to perform this initial step. A translation group (eight persons) including methodologists, linguists, psychologists, and practitioners in palliative care was created.

The translation into French and validation of the English-language QUAL-E and MVQOLI questionnaires were not done using backwards translations. Some studies underlined that backwards translation methods could generate a 'word by word' translation instead of fluent, natural, and appropriate language [31].

The selected translation process for linguistic validation included a translation to the target language (French) made by one translator who was a native English speaker. This allowed us to take into account specific intercultural validity problems.

Second step

Before initiating the prospective study, a pre-test will be done in 30 patients to check this translation. Particular attention will be paid to collecting data on patients' understanding of the questions as well as their acceptability. Patients' suggestions and their feelings regarding the QoL questionnaires will be collected.

Furthermore, clinicians specialized in palliative cancer care will also read and comment the proposed French translation.

This step is crucial to assess the cultural adaptation and the weight of the words in this setting. This step is actually ongoing. Agreements with the investigating center have been drafted (November 2010).

### Sample size

#### Primary endpoint

To study the validity of the questionnaires, the selected primary outcome is reproducibility assessed by intraclass correlation coefficients (ICC).

Taking into account the number of dimensions for each QoL questionnaire as well as the number of scores (continuous variable) for which the ICC will be calculated, using an unilateral alpha type one error of 0.001, a power of 80% and the following hypotheses (N'Query:Advisor V7):

H0: an ICC < 0.5 is uninteresting

H1: an ICC ≥ 0.65 is the minimum required for reproducibility

It will be necessary to include 338 patients.

Taking into account that 10% of patients will be lost to follow-up, it will be necessary to include 372 patients.

### Sample size for secondary objectives

The main endpoint to assess the added value of spontaneous QoL completion is the proportion of patients who report at least one Minimal clinically important difference (MCID) using the Jaeschke transition question.

The minimal clinically important difference is defined as an improvement or a deterioration of 5% in the theoretical QoL score range [23].

With a bilateral alpha type one error of 1% (Bonferroni adjustment for multiple comparisons) a power of 90%, and the following hypotheses:

H0: 70% of patients report an MCID before death in arms A and B

H1: 90% of patients report an MCID before death in arms C and D

It will be necessary to have 243 patients with at least two completed QoL questionnaires between two follow-ups representing 65.4% of the 372 patients included for the primary objective.

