QoL will be described at each follow-up and compared at the inclusion (using Wilcoxon rank test) and then longitudinally analyzed using mixed model analyses of variance for repeated measurement [39-41] to test for the following: a therapeutic strategy effect whatever the follow-up; time effect whatever the therapeutic strategy; interactions between therapeutic strategy and follow-up; and effects of other clinical factors. The best model will be chosen according to the smaller Akaike's information criterion (AIC).

As for the TUDD approach, it will be compared with Log-Rank tests. Univariate and multivariate Cox analyses will be done to compute hazard ratios with 95% CI.

3. To assess the added value of spontaneous QoL completion to detect a clinically significant change in this setting

The proportion of patients who report at least one MCID during follow-up using the Jaeschke transition question will be compared according to the group allocated by randomization using univariate and multivariate logistic regressions.

We will also compute effect size (ES) and standardized response mean (SRM) to explore sensitivity to change according to spontaneous completion of a QoL questionnaire or not. We aim to demonstrate that with spontaneous completion of QoL questionnaires, ES and SRM will be improved.

For the sensitivity analysis, time to definitive QoL deterioration will also be estimated including this spontaneous completion of QoL questionnaires.

Analyses will be performed on an intent-to-treat principle.

4. To assess the effect of questionnaire order on QoL levels Longitudinal QoL analyses will be done as described above QoL will be described at each follow-up and compared at inclusion and then longitudinally analyzed using the mixed model analysis of variance for repeated measurements [39-41]. For the TUDD approach, it will be compared with Log-Rank tests. Univariate and multivariate Cox analyses will be done to compute hazard ratios with 95% CI.

Analyses will be performed on an intent-to-treat principle.

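### The objective 3 endpoint relies on a transition question that Table 1 does not schedule after randomization in arms A and B, and the MCID it counts is defined in two ways

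*Protocol article*

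**What the plan says.** Under Sample size for secondary objectives, the main endpoint for spontaneous completion is "the proportion of patients who report at least one Minimal clinically important difference (MCID) using the Jaeschke transition question". The hypotheses are 70% before death in arms A and B against 90% in arms C and D, with two-sided alpha 1% and 90% power, and the requirement is "243 patients with at least two completed QoL questionnaires between two follow-ups".

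The analysis text for objective 3, under Longitudinal analyses, repeats the endpoint: "The proportion of patients who report at least one MCID during follow-up using the Jaeschke transition question will be compared according to the group allocated".

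Table 1, under Randomization, has a row named "Responsiveness question". It shows all four arms at day 1 and at the retest, nothing in the monthly follow-up column, and arms D and C in the column headed "If necessary according to randomized allocated arm (notebook)".

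Completion of QoL questionnaire describes the booklet for arms C and D, handed out after randomization, which contains "the perception of QoL changes using the Jaescke transition question". The last paragraph of that section lists the transition question among other data to be collected, as a means of establishing the MCID, without naming arms or visits.

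Directly after the endpoint, the sample size section adds: "The minimal clinically important difference is defined as an improvement or a deterioration of 5% in the theoretical QoL score range".

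**The concern.** A comparison of A+B with C+D needs the outcome measured after randomization in both groups. On the Table 1 schedule the transition question is put only to C and D after randomization, and there only when a patient chooses to fill in the notebook. If sites follow that schedule, any contrast shows who was asked, not what spontaneous completion adds.

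The second MCID definition makes this worse. A patient's own rating of change and a computed change of 5% of the score range can classify the same patient differently. If the transition data prove to be missing in A and B, the score rule is the obvious substitute, but nothing ties the planned 70% and 90% to it. An unasked transition question cannot be recovered later, least of all from patients who have died.

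**Working it through.** **1. The planned size.** Inputs from Sample size for secondary objectives: p1 = 0.70, p2 = 0.90, two-sided alpha 0.01, power 0.90. Allocation is 1:1:1:1 (Randomization), so A+B against C+D is 1:1.

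Pooled normal formula, per group:

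n = [z(0.995)·√(2·0.8·0.2) + z(0.90)·√(0.7·0.3 + 0.9·0.1)]² / 0.2²
= [2.576·0.5657 + 1.282·0.5477]² / 0.04 = 116.5, so 117 per group and 234 in total.

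With continuity correction: 126.3, so 127 per group and 254 in total. Fisher's exact test with 122 per group (244 in total) has 89.9% power. The stated 243 lies within this range, and the normal approximation gives 91.4% power at 243. The arithmetic is sound, and 243 is a total over both groups.

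**2. Where the endpoint would be recorded.** I take the responsiveness question in Table 1 to be the Jaeschke transition question. No other item in the article fits, and its notebook entry matches the booklet described for C and D.

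| Occasion | Relative to randomization | A and B | C and D |
|---|---|---|---|
| Day 1 | before | yes | yes |
| Retest | before | yes | yes |
| Monthly visits | after | blank | blank |
| Notebook | after | not given | if the patient completes it |

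Recruitment states that randomization follows the retest, so the first two rows cannot supply a follow-up outcome. Scheduled post-randomization administrations in A and B: 0. Patients concerned: 372 / 2 = 186.

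**3. The two definitions.**

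| | Transition question | 5% of score range |
|---|---|---|
| Source | patient's rating of change | difference between two scores |
| Post-randomization data in A and B per Table 1 | none scheduled | monthly scores from all three questionnaires |
| Named as endpoint for objective 3 | yes, twice | no |
| Linked to 70% and 90% | not stated | not stated |

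**4. Number of occasions.** Even with the question asked monthly in every arm, C and D have additional notebook occasions. As an illustration, assume (the article gives no such figures) independent forms with an equal chance p of registering a change, two per patient in A and B and four in C and D. If two forms give 70%, then 1 − (1 − p)² = 0.70, so p = 1 − √0.30 = 0.45. Four forms give 1 − 0.30² = 0.91. Extra occasions alone could therefore produce a contrast about as large as the planned one.

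**The case against.** The strongest reply is that one blank cell in a table read from PDF is thin evidence. Footnote c has no visible anchor in the table, so some markup was lost. The row also places a change question at day 1, when there is nothing earlier to compare with, so the whole row may be misplaced. The list of other data has no arm restriction, and the 70% hypothesis and the objective 3 analysis both presuppose data in A and B. The booklet text does not say the question appears only there. The article is a condensed document and the case report form is not shown.

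This stands as far as intent goes: collection in all arms may well have been meant. It does not remove the conflict. The other follow-up rows use a distinct notation for the monthly column, and the responsiveness row has no such entry. Its notebook entry agrees with the separate booklet text. An unscheduled mention does not override an explicit schedule.

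It is also fair that the 5% rule can be computed in every arm, so some comparison remains possible; it is just not the endpoint named. And detecting changes between visits is the stated purpose of this randomization, so more opportunity to register change is partly the effect under study and not simply bias.

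**Conclusion.** The point holds as a contradiction within the document. The objective 3 endpoint requires post-randomization transition answers in all arms, while Table 1 and the booklet description provide them only in C and D. Followed literally, the schedule leaves about 186 of 372 patients without endpoint data and the 70% control rate unobservable. Separately, two different measures are called the MCID, and the hypothesized rates are not assigned to either. This rests on the responsiveness question being the transition question and on the monthly cell being truly blank.

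Several stronger readings are tempting but not supported:

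- That the data were certainly not collected in A and B. The unscheduled listing leaves this open.
- That the evaluable set consists of patients with between-visit forms, and so depends on allocation. The 243 is a two-group total and exceeds the 186 patients in C and D, so at least 243 − 186 = 57 would have to come from A and B. The phrase must mean questionnaires available in every arm.
- That the intent-to-treat statement destroys the power. "Analyses will be performed on an intent-to-treat principle" does not say that non-evaluable patients count as having no MCID, and a power loss derived from that rule would be invented.
- That under the 5% rule nearly every patient qualifies. This needs a rule of any one among several independent scores, which the article never states.

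The objective is secondary. The primary test-retest ICC is measured before randomization and is not affected. The point still needs correcting, because this comparison has its own power calculation and missed answers cannot be retrieved.

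**What to change.** - Enter the transition question in the monthly follow-up column of Table 1 for all four arms, and make the data-collection paragraph agree with it.
- Define the objective 3 endpoint by the transition question: at least one reported change after randomization, counting monthly answers in all arms plus notebook answers in C and D. Notebook answers belong in the endpoint, since between-visit detection is what the randomization tests.
- State that the 70% and 90% refer to this endpoint, and make the 5% score change a supportive analysis.
- Acknowledge that the notebook gives C and D more occasions to register a change, and add a supportive comparison on monthly answers only.

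The cost is one extra item per monthly visit for a frail population, a change to the monthly form and revised endpoint wording. At submission 12 of 372 patients had been included, so 360 of the planned patients could be followed under the corrected schedule. No new sample size follows, because the planned rates are unchanged.
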